### **1.1 Statistical analysis and Sample size**

Trial will be prospectively registered on ANZCTR.

Efficacy of intervention will be analysed on an intention to treat basis. The analysis population is the intention to treat population defined as all study participants except for those who do not consent to use of data. There will be no imputation for missing data. A per protocol analysis will also be conducted including all participants with adherence to study medication of >80% of total study duration.

Normally and non-normally distributed data will be presented as mean and standard deviation (SD), and median and interquartile range (IQR), respectively. Between-group comparison of parametric data will be provided as mean difference and confidence interval and analysed using Student's t test. Between-group comparison of non-parametric data will be presented at median difference and analysed using the Mann-Whitney U test. For dichotomous data, frequencies and percentages will be presented and between-group analysis will use Fischer's Exact or Chi-squared test as appropriate. The numbers at risk in each group and the number and proportion of events observed will be reported, as well as the equivalent absolute risk difference, relative risk ratio and corresponding 95% confidence intervals. Survival time from randomisation until day 60, according to treatment group will be displayed as Kaplan-Meier curves and analysed using a log-rank test. Estimates of hazard ratios for survival, with corresponding 95% CI and P values, will be obtained from the Cox proportional hazards models incorporating treatment group alone, and independent covariates used in the multivariate models. Secondary analysis will also be conducted adjusting the primary outcome variable for prespecified baseline covariates (age, gender, APACHE-II score, BMI) in a transformed multivariable linear regression model including

baseline univariate variables with a  $p < 0.05$ . For all outcome analyses a two-sided P value of  $< 0.05$  will be considered significant.

Baseline variables recorded to demonstrate that the groups are comparable; if this is not demonstrated, *post-hoc* adjustments to correct for differences will be applied.

Sample size calculation: 60.

This is based on several different assumptions and outcome measures:

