## **METHODS: ASSIGNMENT OF INTERVENTIONS**

### **Sequence generation**

A permuted block randomisation method will be used with variable block sizes, stratified by site.

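### The adjusted model is chosen from the trial data (a univariate p<0.05 screen and a criterion-free post-hoc imbalance rule); as a lesser point, site is a randomisation stratum but enters no stated analysis.

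*Protocol*

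**What the plan says.** All the analysis rules are in the Protocol, section 1.1 (Statistical analysis and Sample size).

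- **Main comparisons.** These are unadjusted: "Between-group comparison of parametric data will be provided as mean difference and confidence interval and analysed using Student's t test", with non-parametric data "presented at median difference and analysed using the Mann-Whitney U test". Fisher's exact or chi-squared tests are given for dichotomous data, and log-rank and Cox methods for survival to day 60.
- **Adjusted analysis.** "Secondary analysis will also be conducted adjusting the primary outcome variable for prespecified baseline covariates (age, gender, APACHE-II score, BMI" are to be used "in a transformed multivariable linear regression model including" "baseline univariate variables with a" p-value below 0.05. The Cox model also takes its covariates from the multivariable models.
- **Baseline imbalance.** "Baseline variables recorded to demonstrate that the groups are comparable; if this is not demonstrated", then post-hoc "adjustments to correct for differences will be applied". No criterion, variable list or model is given, and the sentence is not limited to secondary analyses.
- **Randomisation.** Under Sequence generation: "A permuted block randomisation method will be used with variable block sizes, stratified by site". Site is not named as a covariate or stratum in any test or model of section 1.1. Hospital appears in the analysis text only as a source of unit costs for the economic evaluation.

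**The concern.** A covariate list is prespecified only if the results cannot change it. Here one sentence names four covariates and then brings in a significance filter. If the filter acts on the four, some may be dropped. If it adds to them, any collected baseline variable may enter. An analyst following the text could defend several different models.

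The imbalance rule has the same weakness. Under correct, concealed randomisation, baseline differences are due to chance, so the rule makes adjustment depend on chance. Because no criterion is given, it also depends on judgement exercised after the data are seen. At stake are the credibility of any adjusted result and the power lost when useful covariates are screened out.

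Site raises a separate and smaller question. Stratified allocation balances the arms within site, but an analysis that ignores site leaves between-site variation in the error term and gives up the precision that the design provides.

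**Working it through.** **Inputs from the protocol.** Total 60 with 1:1 allocation, so 30 per group; two-sided 5% level; four units have expressed interest; length-of-stay difference 3 days with IQR 5.4.

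**Assumptions, not in the documents.** Four sites of 15; the share of outcome variance due to site (0, 10, 20%); covariate correlations and R²; independence of baseline variables; p<0.05 as the imbalance trigger.

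**The plan's own figures.** The plan gives no figure for adjustment. Its 24 per group for walking (27% against 67%, reading the 40 as percentage points) reproduces with the pooled-variance formula, and 48/0.8 = 60 corresponds to 20% loss. For scale, the length-of-stay assumptions give SD = 5.4/1.349 = 4.0 and d = 3/4.0 = 0.75. That d is used below with all 60 patients. The plan's 24 per group for length of stay does not reproduce at two-sided 5% (28 are needed), but nothing here depends on that.

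**1. Reliability of the screen.** For a true correlation of 0.25, Fisher's z = atanh(0.25) = 0.2554. Multiplied by √(60−3) = √57 this is 1.93, and the chance of exceeding 1.96 in absolute value is 0.487. A moderately prognostic covariate is therefore kept in about 49% of trials.

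**2. Chance imbalance.** The probability of at least one p<0.05 among k independent baseline variables is 1 − 0.95^k:
- k = 4: 18.5%
- k = 20: 64.2%

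**3. Effect of the data-driven rules.** Simulation: 60 patients, blocks of 2 and 4 within four sites, 4 or 20 candidate covariates with joint R² 0 or 0.3, no site effect, 6,000 runs per setting.

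| Analysis | Type I error |
|---|---|
| Screened model alone | 4.7–5.3% |
| Imbalance-triggered adjustment alone | 4.0–5.3% |
| Smallest p of unadjusted, fixed, screened and imbalance-adjusted | 6.0–9.4% |

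Power at an effect of 0.735 SD, with four covariates of joint R² 0.3: 80.5% unadjusted, 84.7% screened, 89.5% with all four always entered.

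**4. Omitting site.** Let R² be the share of variance due to site. Within-site balance makes the true variance of the treatment difference (1−R²) times what the unstratified test assumes. The t critical value is 2.002 (58 df).
- Actual level of the unadjusted test = P(|t₅₈| > 2.002/√(1−R²)).
- Signal = 0.75/√(2/30) = 2.905. Power without site = P(noncentral t₅₈ with mean parameter 2.905/√(1−R²) exceeds 2.002/√(1−R²)).
- Power with site uses the same noncentrality, 55 df (60 − 1 − 1 − 3) and critical value 2.004.

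| Site share (assumed) | Cut-off 2.002/√(1−R²) | Actual level without site | Power without site | Power with site |
|---|---|---|---|---|
| 0% | 2.002 | 5.0% | 81% | 81% |
| 10% | 2.110 | 3.9% | 83% | 85% |
| 20% | 2.238 | 2.9% | 84% | 89% |

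Simulation agrees: 3.8–4.2% at a 10% share and 3.0–3.2% at 20%. Pairing the t cut-off with a normal tail would give 3.5% and 2.5%, but that calculation returns 4.5% at zero share, so it is not used.

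**The case against.** The strongest defence has four parts.

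- **The screen sits in a labelled secondary analysis.** The main t and Mann-Whitney comparisons are unadjusted. This stands: the screen does not decide the main test. A reader might also infer that the screened model is anti-conservative because its standard errors ignore the selection. The simulated level of 4.7–5.3% does not support that. The 6.0–9.4% arises only if the most favourable of four analyses is reported, which the protocol does not propose. The defence does not cover the imbalance sentence, which is not confined to secondary analyses.
- **The 64% is not a forecast.** It needs 20 independent variables and a significance trigger. The protocol states no trigger, and some recorded variables, such as the several severity scores, are likely to be correlated. This stands, so the figure should be read only with its conditions and beside the 18.5%.
- **Site may be left to the SAP.** The protocol is silent on site and does not exclude it, and an SAP could add it. This stands and makes site the lesser point. A reader might infer that omitting site inflates false positives, but the direction is the opposite. If site explains nothing, nothing is gained by including it.
- **The primary test need not change.** A reader might conclude that a site-stratified rank or time-to-event test is now required. It is a reasonable option, but the fault lies in how covariates are chosen and does not require a new primary test.

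An SAP could not quietly repair the screen or the imbalance rule, because both are written into the protocol. An SAP with a fixed model would contradict that text.

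**Conclusion.** The point holds for the two stated rules. The adjusted model is described as prespecified but depends on the data on either reading of the sentence, and the imbalance rule has no criterion and no boundary. The consequence is analyst freedom and lost power: about 5 points (89.5% against 84.7%) if four covariates jointly explain an assumed 30% of variance. It is not material type I inflation of the screened model on its own.

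The site omission is secondary and errs on the safe side. It costs nothing at a zero site share, and about 2 to 5 points of power at an assumed 10–20% with d = 0.75 and 30 per group. The documents give no site share, so these are illustrations over a range. This should be corrected, but it does not invalidate the main comparison.

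**What to change.** 1. Delete the univariate p<0.05 rule.
2. Delete the imbalance-triggered adjustment, or label it exploratory. Baseline characteristics are then described and not used to choose the model.
3. For both listed primary outcomes (time to walking with one assist, and hospital length of stay), fix the adjusted model as treatment, site, age, sex, APACHE-II and BMI, all entered regardless of p-value.
4. State a rule for pooling very small sites.
5. Optionally, use a site-stratified version of whichever primary test is adopted.

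The cost is protocol wording and a few degrees of freedom. With four sites the model has 1 + 1 + 3 + 4 = 9 parameters, leaving 51 residual degrees of freedom from 60 patients. The four covariates are already collected and site is known from randomisation. The change should be made before unblinding.

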### **HYPOTHESES:**

Nandrolone will improve muscle strength and physical functioning at hospital discharge and at follow-up 3 months after enrolment.

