### **Outcomes**

#### **Primary and secondary outcomes**

Primary outcome:

1. Time to walking with one person assisting (days from admission to ICU).
2. Hospital length of stay

Secondary outcomes:

1. Change in muscle strength as measured by the medical research council muscle strength (MRC) sum score - enrolment to discharge (note some ICU patients may not be able to participate in full MRC scoring, score will be extrapolated from available limbs) (9)
2. Grip strength (measured by hand held dynamometry)

3. Functional activity at hospital discharge (measured by physiotherapy staff using the Chelsea critical care physical assessment tool (CPAx (7)) and follow-up phone call at 3 months post discharge (using SF-36).
4. Hospital length of stay
5. Time to return to work (days) (for those working pre ICU).

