1. Hospital length of stay, as sample of  $n=24$  per group has 80% power to detect a median difference of 3 days LOS (26 vs 23 days) with IQR 5.4 between independent groups (this is a conservative estimate as in the pilot, LOS results were 26 vs 36 days).
2. Time to walking with one-assist (ICU mobility scale). A sample of 24 per group has 80% power to detect a difference in proportions of 40 between the intervention and control groups, of patients walking with one assist at discharge (from a baseline of 27% in pilot).

To allow for loss to follow-up, the sample size number increased to 60.

Subgroup analysis: due to potential heterogeneity in patients, stratification based on MRC score,  $\geq 48$  (48 is an accepted cut off for ICU acquired weakness).

Economic evaluation:

An economic evaluation will be performed. Cost offsets from any reduction in LoS will be estimated separately for ICU stay and total hospital stay, and costed using hospital-specific per day costs. We will estimate QALYs using the SF-36 data converted to SF-6D using Australian population weights.(6)

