## **DATA COLLECTION, MANAGEMENT, AND ANALYSIS**

### **Data collection methods**

#### **Data Collection**

Data will be collected on a prespecified eCRF (RedCap - Research Electronic Data Capture - a secure web application for building and managing online surveys and databases) supported by a study-specific data dictionary and including checks of logical consistency and automatic query generation.

The following data will be collected:

- Age
- Gender
- ANZICS APD number

- Admission type (elective vs. emergency)
- ICU admission source (i.e. Emergency Department vs. ward vs. theatre vs. other hospital)
- Chronic APACHE co-morbidities
- APACHE-III admission diagnosis
- Illness severity based on the on the APACHE-II and III scores and risk of death, and “ANZ Risk of Death” models score
- ICU or HDA mortality
- ICU or HDA LOS
- Total duration of mechanical ventilation
- Total duration of vasoactive medication requirement
- Incidence and duration of renal replacement therapy
- Hospital mortality
- Post-ICU ward LOS
- Hospital disposition (home vs other acute care facility vs rehabilitation)
- ICU readmission
- Hospital readmission
- Day 60 mortality
- Inflammatory markers (CRP, Procalcitonin and WBC count at enrolment, ICU discharge and hospital discharge)
- BMI, weight at hospital admission, pre-admission medications.
- Baseline SF-36, FIM score and Barthel Index, to determine the patient’s pre-existing functional status (based on status two weeks prior to admission to ICU, from patient or surrogate).
- **Measurement of variables:**
  - **1. Laboratory tests**
    - Pregnancy test in women of child bearing age
    - Baseline: sex hormone binding globulin, testosterone.

- Routine blood tests will occur as planned by treating clinicians, and will collect:
- Haemoglobin, white cell count, albumin, urea and creatinine, alanine transferase.
- Lipids at baseline and at day 15-21.
- **2. Strength and weight measurements**
- a) Weekly: Hand grip strength, weight (kg) and MRC.
- **3. Other measures**
- Physiotherapy received - Duration of rehabilitation physiotherapy and mobility achieved (ventilation physiotherapy treatments will not be counted).
- Nutrition received - Caloric intake (kcal/total), Protein intake (g/total), Food intake (% of meals).
- **Follow-up**
- Phone call follow-up at 3 & 6 months using the SF-36 score , and asking about return to work (see script page).

*Pre-specified Subgroups:*

BMI at enrolment < 20

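### The protocol calls any outcome with p<0.05 significant, while muscle strength and 3-month function, central to its hypothesis, are measured only by secondary outcomes

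*Protocol*

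**What the plan says.** Four places in the Protocol bear on this.

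- **Threshold (1.1 Statistical analysis and Sample size).** "For all outcome analyses a two-sided P value of" less than 0.05 is to count as significant. The sentence does not separate primary from secondary outcomes, and the Protocol nowhere orders the outcomes, divides the alpha or labels any outcome exploratory.
- **Hypothesis (1.2 Objectives, Hypotheses).** The only hypothesis is "Nandrolone will improve muscle strength and physical functioning at hospital discharge and at follow-up 3 months after enrolment". The background section likewise describes the project as a test of whether nandrolone improves muscle strength.
- **Outcomes (Primary and secondary outcomes).** Two are listed as primary: "Time to walking with one person assisting (days from admission to ICU") and "Hospital length of stay". The secondary list has "Change in muscle strength as measured by the medical research council muscle strength (MRC) sum score", grip strength, "Functional activity at hospital discharge (measured by physiotherapy staff using the Chelsea critical care physical assessment tool"; CPAx) with a follow-up SF-36 at 3 months, length of stay again, and time to return to work.
- **Subgroups.** The sample size section plans a subgroup analysis: "due to potential heterogeneity in patients, stratification based on MRC score", with a cut at 48. The data collection section adds "BMI at enrolment < 20" and three admission causes. No method of testing is given for any of them.

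**The concern.** The threshold sentence lets each secondary p value be called significant, and the hypothesis is worded in terms that several secondary outcomes address directly. In a trial of 60 patients, walking time and length of stay could both be null while one of MRC change, grip, CPAx or SF-36 falls below 0.05. Under the Protocol's own wording that result would be significant and would match the written hypothesis. A claim reached that way does not carry a 5% error rate, because several outcomes each had a chance to produce it. The secondary label gives weaker protection than usual when the hypothesis itself names what the secondary outcomes measure.

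**Working it through.** **Inputs from the Protocol.** Two-sided alpha of 0.05 for each outcome. Four secondary outcomes that bear on the hypothesis: MRC change and grip (strength), CPAx at discharge and SF-36 at 3 months (function). Each is counted as one test. That is a low count: grip has no fixed time point although it is measured weekly, and no SF-36 scale is named.

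**Input assumed.** The correlation ρ between the test statistics is not in the Protocol. It is taken as equal for all pairs and varied from 0 to 0.7, with 0.8 as a further check.

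**Stated figure.** The Protocol gives no familywise error rate, so there is none to reproduce. The only reference value is the 0.05.

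**Independent tests.** The chance of at least one p<0.05 among k tests with no drug effect is 1 − (1 − 0.05)^k.

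- k = 4: 1 − 0.95⁴ = 1 − 0.8145 = 0.1855, or 18.5%. Ratio to 5%: 3.7.

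**Correlated tests.** Write each statistic as √ρ·U + √(1−ρ)·Eᵢ, with U and Eᵢ independent standard normal. The chance that at least one exceeds 1.96 in absolute value is

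1 − ∫ [Φ((1.96 − √ρ·u)/√(1−ρ)) − Φ((−1.96 − √ρ·u)/√(1−ρ))]⁴ φ(u) du.

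| ρ (assumed) | At least one p<0.05 among four | Multiple of 5% |
|---|---|---|
| 0 | 18.5% | 3.7 |
| 0.3 | 17.4% | 3.5 |
| 0.5 | 15.6% | 3.1 |
| 0.7 | 13.0% | 2.6 |
| 0.8 | 11.4% | 2.3 |

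Simulation with 400,000 draws per setting agrees to within about 0.1 percentage point.

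**Which outcome tests which part of the hypothesis.**

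| Part of the hypothesis | Primary outcome that bears on it | Secondary outcomes that bear on it |
|---|---|---|
| Muscle strength | none | MRC change, grip |
| Function at discharge | time to assisted walking | CPAx |
| Function at 3 months | none | SF-36 |

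Length of stay, the other primary outcome, measures neither strength nor function.

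**The case against.** **The hypothesis is not left to secondary outcomes alone.** A reader might infer that no primary outcome addresses it. That goes too far. Walking with one person's help is a measure of physical function, and its sample size is based on the proportion who can do so at discharge. This objection stands, and the point is confined to strength and 3-month function.

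**The aims already rank the outcomes.** Aims 1 and 2 are walking and length of stay, and Aim 4 only sets out to document changes in strength. This is fair, and it shows which outcomes were meant to lead. But the aims do not limit the threshold sentence, and the hypothesis gives strength a leading place.

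**The Protocol never says that one secondary result confirms the hypothesis.** This is also fair. It says only that the p value counts as significant, so the error rates above are conditional on someone reading the results that way. The wording permits that reading and does nothing to prevent it.

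**Ordering of secondary outcomes belongs in a statistical analysis plan.** The lack of an order in the Protocol is indeed no finding. The finding is a sentence that the Protocol does contain. A hierarchy in a separate plan would contradict that sentence, so the sentence needs changing in either case.

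**The size could be put higher.** A reader might infer an inflation of three to five times. The four relevant tests give 2.6 to 3.7 times for correlations of 0 to 0.7. Adding return to work gives 1 − 0.95⁵ = 22.6% (4.5 times) if the tests are independent, but return to work is not part of the hypothesis. A reader might also want an error rate for the subgroups. The Protocol describes no subgroup test and gives no subgroup sizes, so no such figure can be supported. That the 0.05 rule reaches subgroups at all is an inference from the words of the threshold sentence.

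**Conclusion.** The point holds in a limited form. The Protocol declares every outcome analysis significant at 0.05, while strength and 3-month function, both central to its hypothesis, rest on secondary outcomes. If a single positive result among the four relevant secondary outcomes were read as support for the hypothesis, the false-positive chance would be about 13% to 18.5%, not 5%. This rests on four tests, equal pairwise correlations between 0 and 0.7, and no drug effect on any of the four; the correlations are assumptions. The excess shrinks as correlation rises but is still more than twofold at 0.8.

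These figures leave out the two primary outcomes. Having two with no stated rule for combining them is a separate multiplicity question (1 − 0.95² = 9.75% if independent). It matters here only because it limits which remedy can be used.

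**What to change.** 1. In the statistical analysis section, replace the blanket threshold sentence with one that applies the two-sided 0.05 level to the primary analysis only.
2. State that secondary outcomes are reported as estimates with 95% confidence intervals, labelled exploratory, with no claim of significance. The section already asks for intervals for several types of outcome, so part of this is in place.
3. State that subgroup results are reported as treatment-by-subgroup interaction estimates with 95% confidence intervals, also labelled exploratory.
4. Reword the hypothesis so that the main one matches the listed primary outcomes, with strength and 3-month function as secondary hypotheses.
5. If a confirmatory claim on strength or function is wanted, a fixed testing order could follow the primary analysis. It cannot operate until the Protocol says how the two listed primary outcomes determine success, so that rule must come first.

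Items 1 to 4 change wording only and need no further patients or data. They should be settled before results are known, since an order or label chosen afterwards cannot protect the error rate. The downside is that an isolated secondary or subgroup p<0.05 could no longer be presented as confirming the hypothesis.

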## **1.3 Trial design**

This study is a multicentre, parallel group, placebo-controlled, randomised, superiority trial which will allocate ICU patients in a 1:1 ratio to nandrolone in addition to standard care compared with placebo in addition to standard care.

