## **2.3 Interventions**

### **2.3.1 Study interventions**

#### *Intervention*

Standard care (see below) with the addition of IMI nandrolone.

Dosing: Males: 100 mg weekly. Females: 50mg weekly – for 3 weeks or until hospital discharge, whichever is earlier.

The study drug will be drawn up by the ICU pharmacist, and then the syringe will be covered (to mask the contents of the syringe). All investigators, clinicians, nursing staff and patient are blinded.

NOTE: Dose change from the pilot study. The dosing was 200mg males/ 100mg females – however this is a large intramuscular volume, and can be difficult in patients without much muscle mass.

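### At the two-sided 5% level that the protocol fixes, 24 per group gives about 70% power for the length-of-stay difference, not the stated 80%, if stays are roughly normal or log-normal

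*Protocol*

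**What the plan says.** Hospital length of stay is listed under the primary outcome in the protocol's Outcomes section, and it is the first of two bases given for the sample size. In 1.1 Statistical analysis and Sample size, item 1 says that 24 per group "has 80% power to detect a median difference of 3 days LOS (26 vs 23 days) with IQR 5.4 between independent groups". The same section sets the significance level: "For all outcome analyses a two-sided P value of" below 0.05 counts as significant. It names Student's t test for parametric data and the Mann-Whitney U test for non-parametric data. Section 1.3 Trial design says that the trial "will allocate ICU patients in a 1:1 ratio". After the two bases, each giving 24 per group, the protocol adds: "To allow for loss to follow-up, the sample size number increased to 60". It states no loss rate, no SD, no distribution for length of stay, no source for the IQR, and no one-sided level for this calculation.

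**The concern.** Every input needed to check the 80% is in the protocol except the shape of the distribution. On the usual conversion of an IQR to an SD, the target is three quarters of a standard deviation, and 24 per group is too few for 80% power in a two-sided 5% test. The stated power of a primary outcome would then be wrong at the number the plan treats as sufficient. The increase to 60, described as cover for loss, would instead be about the number needed to reach 80% at all.

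**Working it through.** **Inputs from the protocol.** Difference 26 − 23 = 3 days; IQR 5.4 days; 24 per group; 1:1 allocation; two-sided 5%; t test or Mann-Whitney; total raised from 2 × 24 = 48 to 60.

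**Assumption.** The protocol gives no SD. For a normal shape the IQR is 1.349 SD, so SD = 5.4/1.349 = 4.00 and d = 3/4.00 = 0.75.

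**Reproducing the plan's figure.** With a one-sided 5% test, the t test needs 22.7 per group for 80% power. The usual Mann-Whitney factor π/3 = 1.047 gives 22.72 × 1.047 = 23.8, that is 24. Power at 24 per group is then 80.3%. So 24 and 80% reproduce, but only one-sided.

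**The same inputs, two-sided 5%.**
- Normal approximation: n = 2(1.960 + 0.842)²/0.749² = 28 per group. Power at 24: 0.749 × √12 − 1.960 = 0.64, which gives 74%.
- t test (noncentral t): 28.9, so 29 per group for 80%. Power at 24 is 72.0%.
- Mann-Whitney (t-test size × π/3): 30.3, so 31 per group. Power at 24 is 69.9%. Noether's formula is slightly lower, at 68%.
- Simulation, 20,000 replicates, Mann-Whitney at 24 per group: 69.3% for normal data, and 69.0% for log-normal data with medians 26 and 23 and IQR 5.4.

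| Per group (two-sided 5%) | t test | Mann-Whitney |
|---|---|---|
| 24 | 72% | 69-70% |
| 30 | 81% | 79-80% |

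**The loss allowance.** Going from 48 to 60 implies a loss of 1 − 48/60 = 20%. The two-sided need with no loss is 2 × 29 = 58 by t test or 2 × 31 = 62 by Mann-Whitney. Sixty therefore leaves two patients to spare by t test and none by Mann-Whitney. A full 20% loss would bring the trial back to 24 per group and the first row of the table.

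**Sensitivity to shape.** With the IQR held at 5.4 and 24 per group, symmetric shapes with heavier tails give less Mann-Whitney power: logistic 65%, Laplace 58%. A flat uniform shape gives 85%. Strongly right-skewed shapes shifted by 3 days can reach about 80% by Mann-Whitney: exponential 80%, shifted log-normal with sigma 1 79%, gamma with shape 2 76%. At 30 per group these three give 88%, 88% and 85%. They need a floor close to the median. For the exponential, the scale is 5.4/ln 3 = 4.92 and the median lies 4.92 × ln 2 = 3.4 days above the floor, so almost no stay could be shorter than about 20 days in a group with median 23.

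**The other basis.** Read as 27% against 67%, the walking calculation does reproduce: 24 per group, 81% power, without continuity correction. The fault is confined to the length-of-stay item.

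**The case against.** The strongest reply is that the trial randomises 60, not 48. Length of stay is an in-hospital measure, study data come from medical records (Confidentiality section), and the analysis population is everyone except those who refuse use of their data. Missed telephone calls cost SF-36 and return-to-work data, not length of stay. This stands, and it limits the consequence. A reader might infer that the trial as planned is underpowered for length of stay, or that 70 to 78 patients are needed. The documents do not support that: those totals apply the implied 20% loss to an outcome that hardly depends on follow-up, and near 30 per group the power is about 80%.

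Second, the 69-72% depends on a shape that the protocol does not state, and a median, an IQR and a Mann-Whitney test suggest skewed data. This stands in part. It would be wrong to say that no skewed shape reaches 80% at 24 per group. But the shapes that do need a floor 3 to 4 days below the median, and the eligibility criteria set none: they ask for an ICU or HDU stay of at least 5 days, or significant weakness. An ordinary log-normal with the stated medians and IQR gives 69%.

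Third, the protocol calls its estimate conservative because the pilot showed 26 against 36 days. A reader might infer that the label is wrong, since of the pilot the protocol says "The dosing was 200mg males/ 100mg females", twice the present amounts, or that an IQR of 5.4 is implausibly tight. Neither is shown. The protocol discloses the dose change, and a 3-day target is less than a third of the pilot's 10-day difference. The pilot's spread is not in the document. Wider IQRs lower the power sharply, but they would be assumptions of the reader and not errors of the plan.

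**Conclusion.** The concern holds in a limited form. The statement that 24 per group gives 80% power is wrong under the protocol's own two-sided 5% rule, by about 8 points for the t test and 10 to 11 for Mann-Whitney. This assumes a roughly normal or log-normal shape with IQR 5.4. The 80% needs 29 to 31 per group. The planned 30 per group meets this closely (about 80-81%) if nearly all are analysed, so the increase to 60 is not a spare 20% margin for this outcome. That the planners used a one-sided test is only an inference from the matching numbers; the protocol does not say so. The point should be corrected, but it does not call the size or conduct of the trial into question.

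**What to change.** Replace the length-of-stay power statement with one to this effect: for a 3-day difference with IQR 5.4 and a two-sided 5% test, 30 per group with all 60 analysed gives about 80% power, and 24 evaluable per group gives about 70%. Name the test used for the calculation, the distribution assumed in using the IQR, and the source of the 5.4 days. Where the total is raised to 60, make clear that for length of stay this is roughly the number needed with no loss, and that little loss is expected because the outcome comes from hospital records.

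The cost is a text change and a less favourable stated power. No extra patients are needed, and the analysis and conduct stay as they are.
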